### Debriefing

All participants will be debriefed after the end of the study. This will be done by providing them with a report that will include information about the aim of this study and the different intervention conditions, the results of the study and their own performance during the study. It is practically and financially not feasible to organize the cognitively enriched walking intervention again for six months for the PA group and CG. Therefore, all participants will be given access to all intervention materials (e.g. the manual for the coaches) so they can try the cognitively enriched walking by themselves.

## 5. Outcome measures

### 5.1. Effectiveness

The main outcome of this study is cognitive functioning. We chose several outcome measures to assess different aspects of **cognitive functioning**.

- *Cambridge Neuropsychological Test Automated Battery (CANTAB)* (Bento-Torres et al., 2017; Sahakian & Owen, 1992; Zygouris & Tsolaki, 2015): objective cognitive functioning is assessed with CANTAB.

Different tests can be configured in a test battery, based on the focus of the study. The tests are non-verbal and culturally independent and make use of touchscreen technology. The CANTAB has been shown sensitive to changes in cognitive performance. Six different tests were selected to obtain a comprehensive view of one's objective cognitive functioning. The selected tests assess psychomotor speed/attention (i.e. sustained attention), memory (i.e. visual episodic attention and short term visual memory) and executive functioning (i.e. working memory and strategy). This is the primary endpoint of the study

- *Cognitive and Leisure Activities Scale (CLAS)* (Galvin et al., 2021): this is a measure of the type and frequency of cognitive activities. It includes sixteen types of cognitive activities and is self-administered. Even though it is difficult to establish the validity of this new questionnaire since there is no gold standard to measure cognitive activity, it is suggested that this questionnaire has a good content validity. This will be used as a covariate in the analysis.
- *Cognitive Failures Questionnaire (CFQ)* (Broadbent et al., 1982; Ponds et al., 2006): this self-administered questionnaire assesses subjective cognitive functioning. Participants are asked about minor everyday slips or errors. It is not a replacement for testing objective cognitive functioning, but reflects the experience of the frequency of everyday slips of the participant.

### **Psychosocial wellbeing**

- *Beck Depression Inventory (BDI-II)* (Balsamo et al., 2018): this self-administered questionnaire is part of our screening procedure, but will be administered during all measuring points to assess the evolution of depressive symptomatology during and after the intervention. There is evidence supporting the construct, convergent and discriminant validity of the BDI-II.
- *Warwick-Edinburgh Mental Wellbeing Scale (WEMWBS)* (Tennant et al., 2007): this is a measure of wellbeing, focussing on positive mental health. This measure is suggested to be able to assess improvements in mental health wellbeing. This scale has robust psychometric properties.
- *De Jong Gierveld short scale for loneliness* (De Jong Gierveld & Van Tilburg, 2008; De Jong Gierveld & Van Tilburg, 2010): this is a six-item questionnaire with a threefold application. It assesses overall loneliness, as well as emotional loneliness and social loneliness. Good validity and reliability has been reported for this questionnaire.
- *Social Support List – Interaction (SSL 12 – I)* (Kempen & van Eijk, 1995; van Eijk et al., 1994): this is a twelve-item questionnaire with satisfactory psychometric properties that was especially developed for use in older adults. It assesses three dimensions of social support: daily support, support in case of problems and appreciation.
- *Expectations Regarding Aging (ERA-12)* (Sarkisian et al., 2005): this twelve-item questionnaire assesses older adult's expectations regarding aging. It provides us with a general score as well as a separate score for the expectations regarding cognitive, mental and physical health. Acceptable reliability and validity to estimate older adults' expectations regarding aging has been established.

### **Physical activity**

- *International Physical Activity Questionnaire – Short Form (IPAQ-SF)* (Craig et al., 2003): this is an extensively used self-report measure for physical activity during the past seven days. It provides us with a categorical score of physical activity, distinguishing between low, moderate and high levels of physical activity.

- *Actigraph accelerometer at hip (Barnett et al., 2016)*: this is an objective measure of physical activity level, frequently used in physical activity studies with older adults. Participants will be asked to wear this accelerometer during seven days (day and night). They will be asked to register when and why they did not wear the device in a personal diary provided by the researchers. The duration spent in moderate-to-vigorous PA (based on the cutpoints of Barnett et al. (2016)) will be used as an outcome in this study.

### General health

- *The Patient-Reported Outcomes Measurement Information System (PROMIS) eight-item short form for General Health (Pellicciari et al., 2021)*: this is a self-report measure for global self-rated health with acceptable psychometric properties. This questionnaire provides us with a total score as well as distinct scores for mental and physical health.
- *The Patient-Reported Outcomes Measurement Information System (PROMIS) four-item short form for Sleep Disturbances (Buysse et al., 2010; Terwee et al., 2014)*: this self-report measure with good psychometric properties assesses quality of sleep and prevalence of sleep difficulties.

## 5.2. Process evaluation

To gain a meaningful insight into the relation between different components of the new program and the outcomes, we will include a process evaluation. For this, we will use both quantitative as well as qualitative methods. Participants of both the PA+CA as the PA groups will be asked to complete a process evaluation questionnaire after three and six months of the intervention. This will include questions on fidelity, delivered dose (completeness), received dose (exposure, satisfaction), participation rate, acceptability of the intervention, group dynamics, environmental context,...

As the use of both qualitative and quantitative data provides the strongest evidence for process evaluation, we will collect both types of data in this study. Process evaluation tools were developed based on the framework of Saunders et al. (2005), which recommends to evaluate six key elements in a process evaluation: (1) fidelity (quality of the implementation of the intervention), (2) dose delivered (completeness, amount of components provided by the coaches), (3a) dose received – exposure (extent to which participants actively engage with materials), (3b) dose received – satisfaction (participant satisfaction), (4) reach (participation rate), (5) recruitment (procedures used) and (6) context (aspects of the environment that may influence implementation or study outcomes). In the table below, the data sources and data collection tools are summarized.

|    |                               | Data sources             | Tools                                                                                                       | Timing/frequency                                                                                     |
|----|-------------------------------|--------------------------|-------------------------------------------------------------------------------------------------------------|------------------------------------------------------------------------------------------------------|
| 1  | Fidelity (quality)            | Participants and coaches | 
 
Questionnaires and focus groups
 
                           | 
 
Both post intervention
 
                             |
| 2  | Dose delivered (completeness) | Coaches                  | 
 
Questionnaire and focus groups
 
                            | 
 
Both post intervention
 
                             |
| 3a | Dose received (exposure)      | Participants             | 
 
Questionnaire and focus groups
 
Registration form
 
 | 
 
Post intervention
 
During the intervention
 
 |
| 3b | Dose received (satisfaction)  | Participants             | 
 
Questionnaire and focus groups
 
                            | 
 
Post intervention
 
                                  |
| 4  | Reach                         | Coaches                  | 
 
Attendance list
 
                                           | 
 
During the intervention
 
                            |
| 5  | Recruitment                   | Main researcher          | 
 
Documentation of all recruitment activities
 
               | 
 
During recruitment phase
 
                           |

|   |         |                          |                                  |                     |
|---|---------|--------------------------|----------------------------------|---------------------|
| 6 | Context | Participants and coaches | • Questionnaire and focus groups | • Post intervention |
|---|---------|--------------------------|----------------------------------|---------------------|

Table 1. Process evaluation elements, data sources, tools and timing/frequency

### Questionnaires

Questionnaires consist of both closed (Likert scales) and open-ended questions. Separate questionnaires have been drafted for participants and coaches of both intervention groups (i.e., four questionnaires in total: coaches PA only, coaches PA+CA, participants PA only, participants PA+CA). Participants and coaches will receive a link to an online questionnaire (UGent Qualtrics). Coaches are asked to identify themselves by indicating in which city they are guiding a group, and on which days. Furthermore, coaches are also asked to provide sociodemographic information: gender, age and educational degree. The questionnaires for the coaches are attached to this proposal as additional files 1 and 2.

### Focus groups

All participants of the PA only and PA+CA groups will be invited to participate in focus groups. In total, there are four groups performing the PA only program (two in Leuven and two in Ghent) and four groups performing the PA+CA program (two in Leuven and two in Ghent). We will organize eight focus groups for participants, one for each group. Each focus group will consist of 8-13 participants.

There are four coaches guiding the PA only groups and four coaches guiding the PA+CA groups. Therefore, we opted to organize one focus group for the coaches of the PA only groups (from both Ghent and Leuven) and one focus group for the coaches of the PA+CA groups (from both Ghent and Leuven). Each focus group for coaches will thus consist of 4 participants.

Every focus group will take around 60-90 minutes. Focus groups for participants will be organized on campus (in Ghent or Leuven, depending on where participants were part of an intervention group). Focus groups for coaches will be organized on a KU Leuven campus in Brussels (because coaches from Ghent and Leuven will participate in the same focus group). For all focus groups, a semi-structured interview guide will be used. In total, four separate interview guides are prepared: 1) coaches of the PA only groups, 2) coaches of the PA+CA groups, 3) participants of the PA only groups, 4) participants of the PA+CA groups. The PhD student will be moderator of all focus groups, the postdoctoral researcher and/or a master student will be observer. All focus groups will be audio-recorded, and the observer will take notes during the focus groups. The interview guides are attached as additional file 3, 4, 5 and 6.

## 5.3. Procedures

### Screening

A telephone call will be arranged with people interested in participating in this study. During this phone call with one of the researchers, the above-mentioned inclusion and exclusion criteria will be checked. Potential participants that meet the inclusion criteria will be invited for a baseline measurement visit. They will also receive a digital version of the information letter and informed consent, so they can read this before signing it during the baseline visit.

### Baseline visit

First, the informed consent will be signed. At this moment, participants can also ask questions at the researcher if they have any after reading the information letter. During the baseline visit, the MoCA and BDI-II will be administered as a secondary screening for possible cognitive difficulties and depressive symptomatology, respectively. As mentioned above, participants excluded from the study at this stage will be informed about the deviant score by the either the PhD student or the postdoctoral researcher. Furthermore, the person will receive a letter that they can bring at their next appointment with their general practitioner. The letter will (1) contain the description of the test and the score obtained and an explanation that there are multiple possible reasons for such a score, and that only one of them is (mild) cognitive impairment or depressive symptomatology and (2)

indicate that, in case the general practitioner thinks this is necessary, an appointment can be made with a memory clinic or psychologist.

Included participants will be asked to provide sociodemographic information (i.e. age, gender, length, weight, nationality, country of origin, educational level, marital status, longest held profession, and income) during this baseline visit. Furthermore, participants will be asked if there is any relevant medical information the coaches need to know to ensure safety of the waling sessions (i.e., so the coach can anticipate any possibly dangerous situations).

Participants will also be asked to complete the questionnaires regarding cognitive function, psychosocial wellbeing, physical activity and general health described above (see *outcomes*). Objective cognitive and physical activity will be measured at baseline as well by administering the CANTAB and wearing an accelerometer for seven consecutive days (day + night), respectively. Participants will be asked to return the accelerometer by delivering it to the office of one of the researchers or by returning it by post (pre-paid by the research team).

### **Three months visit**

Three months after the start of the intervention, participants will be invited for a second visit. Again they will be asked to complete the questionnaires regarding cognitive function, psychosocial wellbeing, physical activity and general health. The CANTAB will be administered and they will be asked to wear the accelerometer for seven consecutive days. This measurement visit will take place during the intervention period for the PA+CA and PA groups, this will be taken into account in the analysis of the accelerometer data. Furthermore, a process evaluation questionnaire will be given to participants of the PA+CA and PA groups. This questionnaire can be completed at home and returned during the next (cognitively enriched) walking session. Accelerometers can be delivered to the office of one of the researchers or returned by post (pre-paid by the research team).

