## 4. Interventions

As mentioned above, there will be three intervention arms: 1) a cognitively enriched walking program (Physical Activity (PA)+Cognitive Activity (CA)), 2) a walking program without cognitive enrichment (Physical Activity (PA) only) or 3) a passive control group (CG). The passive CG will receive no intervention program. Both the PA+CA and the PA program are group-based and will have a duration of six months (i.e. 24 weeks), with a frequency of two group sessions a week. All group sessions will last for approximately one hour and take place in groups of twelve or thirteen people supervised by a certified coach. Participants in both intervention groups (PA+CA and PA) will be encouraged to do one individual session every week, as well.

The PA+CA group will perform cognitive exercises while walking. One cognitively enriched walking session can be divided in three parts: (1) 5-10 minutes of brisk walking, (2) approximately 30-40 minutes of cognitive exercises while walking and (3) 5-10 minutes of cooling down (i.e. time for small talk or rest and relaxation). Cognitive exercises are exercises that are cognitively challenging and focus on multiple cognitive functions (i.e. attention, memory, executive functions, language, creative thinking) and can be performed while walking. Some examples are: planning a route, solving riddles, noticing, word fluency, bingo (i.e. noticing things along the walk),... These cognitive exercises have been developed in agreement with experts and the target population (Marent et al., 2021). Every cognitively enriched walking session, two to three cognitive exercises will be explained by the coach and performed by the participants. To this end, the coach receives a standardized manual with explanations of the different cognitive exercises. Furthermore, the coach will make sure that participants keep moving while performing the cognitive exercises. For the individual sessions, participants of the PA+CA group will receive practice cards with simplified instructions for all cognitive exercises that can be performed alone, with their partner, friends, or even grandchildren. Participants will be asked to register the number of individual cognitively enriched walks they perform in a personal log-book.

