The PA group will walk for approximately the same amount of time and distance as the PA+CA group, but will not perform cognitive exercises. The coach will supervise and guide the group walk. These participants will also be asked to register the amount of individual walks they perform in a personal log-book.

The passive CG will not receive an intervention. Participants will be informed that they are assigned to the control group.

Participants will receive a letter at home with information about the intervention group they are allocated to (i.e. when will the sessions take place, where will they take place, contact information of the coach). Participants will be asked to be present for as many sessions as possible, but given the real-life context of this study, we will have the coaches track the attendance (in both the PA+CA and PA groups) so we can account for this in the analyses. The control group will receive information about why the use of a control group is important in intervention studies to keep them motivated to attend the following measurement sessions.

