### **Six months visit**

After the end of the intervention, participants will be invited for a third visit. The procedure is the same as that of the second visit. However, participants will not be taking part in an intervention while wearing the accelerometer. Participants will be asked to return the process evaluation questionnaires as well as the accelerometer, either by delivering it to the office of one of the researchers or returning it by post (pre-paid by the research team).

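### The participant process questionnaire has three unreconciled collection routes, and the one written for 3 months runs through a coach-led walk

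*Combined protocol and SAP*

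**What the plan says.** Section 5.2 (Process evaluation) says that participants in both walking arms "will be asked to complete a process evaluation questionnaire after three and six months of the intervention". On content it says: "This will include questions on fidelity, delivered dose (completeness), received dose (exposure, satisfaction), participation rate, acceptability of the intervention, group dynamics, environmental context". Section 2 likewise places questionnaires both mid-intervention and post-intervention.

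The collection route is described in three places:

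- Section 5.2, Questionnaires: "Participants and coaches will receive a link to an online questionnaire (UGent Qualtrics"). No time point is excepted.
- Section 5.3, Three months visit: a questionnaire is given to participants of the two walking arms. "This questionnaire can be completed at home and returned during the next (cognitively enriched) walking session". The sentence that follows offers the office and pre-paid post, but for the accelerometer only.
- Section 5.3, Six months visit: "Participants will be asked to return the process evaluation questionnaires as well as the accelerometer, either by delivering it to the office" of a researcher or by pre-paid post.

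On timing, Table 1 in Section 5.2 lists every participant questionnaire as post-intervention.

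On the sessions themselves, Section 4 says that they "take place in groups of twelve or thirteen people supervised by a certified coach", and for the walking-only arm: "The coach will supervise and guide the group walk". The plan expects attendance to vary: "we will have the coaches track the attendance (in both the PA+CA and PA groups) so we can account for this in the analyses".

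**The concern.** A form that is handed out and physically returned is not an online questionnaire, so site staff cannot follow Sections 5.2 and 5.3 together. The choice matters because of what the form asks. Section 5.2 defines fidelity as the quality of implementation, and the coaches deliver the sessions. A participant who returns such a form at a session that the coach supervises, in a small group, may soften critical answers.

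The 3-month route also depends on attendance. Someone who has stopped walking but still comes to the measurement visit would be given the form, and the one return point named is a session that this person no longer attends. Views from the less engaged are the ones a process evaluation most needs.

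Both mechanisms would push 3-month ratings in the favourable direction. If the two visit descriptions are followed, the route also changes between 3 and 6 months, so a shift in ratings would be mixed with a shift in how they were collected.

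**Working it through.** The point rests on the text, and the plan gives no figure to reproduce. The relevant places side by side:

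| Place | At 3 months | At 6 months |
|---|---|---|
| Section 2 | questionnaire planned | questionnaire planned |
| Section 5.2, opening text | questionnaire planned | questionnaire planned |
| Section 5.2, Table 1 | no participant questionnaire listed | questionnaire planned |
| Section 5.2, Questionnaires | online link | online link |
| Section 5.3, visit descriptions | form given out, returned at next walk | form returned to office or by pre-paid post |

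**Step 1, mode.** The Questionnaires paragraph makes no exception by time point, while the two visit descriptions treat the questionnaire as an object to be returned. No sentence reconciles them.

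**Step 2, timing.** Table 1 leaves out the 3-month administration that Section 2, the opening of Section 5.2 and the Three months visit all include.

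**Step 3, return point at 3 months.** The only one named for the questionnaire is the next walking session. Section 4 makes those sessions coach-led in both arms. The documents do not say who receives the form there, whether it is sealed or coded, or whether the coach can read it.

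**Step 4, alternatives at 3 months.** The office and pre-paid post are offered for the accelerometer at the same visit but are not extended to the questionnaire. At 6 months they are. A suitable route therefore already exists and is simply not written down for the 3-month form.

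**Step 5, who could be affected.** Section 6.2 plans 149 participants allocated 1:1:1, so 149 × 2/3 = 99.3, or about 99 people in the two walking arms. This agrees with eight groups of twelve or thirteen (8 × 12 = 96 to 8 × 13 = 104). It is the number due to receive the questionnaire. The subgroup of interest is those who attend the 3-month visit but have stopped walking, and the documents give no rate for it.

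**Step 6, dependence on the branch.** If the online link is used at 3 months, the concerns about the coach and about non-attenders do not arise. Both are conditional on the return-at-session route.

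**The case against.** The strongest reply is that this is loose drafting with little consequence. The 3-month sentence is permissive, staff might well accept the form with the accelerometer, and the online link would serve anyone who does not walk. The process evaluation carries no hypothesis and is declared exploratory (Section 6.1). Its questionnaire data are only to be described (Section 6.4), and no comparison of 3 with 6 months is planned. There are also eight participant focus groups, moderated by the PhD student and separate from those of the coaches, where critical views can be voiced. Much of this stands, and it limits the point to a small one.

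It also rules out several stronger readings that a reader might infer:

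- *The answers are not confidential.* No sentence says that the coach collects or reads the forms. Only the absence of a stated safeguard is supported.
- *Participants are rating their own coach.* The topics listed include fidelity and satisfaction, but the participant questionnaire is not in the text and no item about the coach is shown.
- *Non-attenders have no way to return the form.* The documents merely state no alternative for the questionnaire at 3 months.
- *About 10 people are lost.* One could take half of the planned 20% dropout: 99 × 0.10 = 9.9. But that 20% is study dropout in the sample-size calculation. A person who has left the trial would not be at the 3-month visit to be given the form, so the return point does not cause that loss.
- *The 3-month ratings will be biased.* This assumes that the paper route is the one used, which the documents leave open.

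What the reply does not remove is the contradiction itself. Nor does it supply a stated safeguard or a second return route at 3 months.

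**Conclusion.** The point holds as an unreconciled inconsistency in mode, return route and timing, with a plausible but conditional risk of bias. If the return-at-session route is used, and no safeguard is added in practice, the 3-month ratings of fidelity, satisfaction and acceptability are at risk of upward bias. The direction is a judgement that rests on two assumptions: that people soften criticism handed in at a coach-led session, and that those who have stopped walking are less satisfied than those who continue. Neither the size of the bias nor the number of people affected can be derived from the documents.

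The change of route between time points would matter only if someone reads the two sets of ratings as a trend. The effect is limited to the exploratory process evaluation. The cognitive primary outcome and the secondary effectiveness outcomes are untouched.

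**What to change.** Label: cheap improvement.

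1. In Section 5.3 (Three months visit), replace the sentence on returning the questionnaire at a walking session.
2. State one route for 3 and 6 months in Section 5.2 (Questionnaires) and in both visit descriptions: the Qualtrics link, sent to everyone allocated to a walking arm regardless of attendance.
3. Name a backup: a paper form that goes back to the researchers by the pre-paid post already planned for the accelerometer.
4. Correct Table 1 so that the timing of participant questionnaires agrees with Section 2, the text of Section 5.2 and the visit descriptions.

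The cost is wording, since the online tool and the pre-paid post are both already planned. The downside is that reminders may be needed and online response may be lower in people aged 65 and over, which is why the paper backup should be written in. If paper is preferred as the main mode, a sealed envelope, or one sentence extending the 3-month post route to the questionnaire, would meet much of the concern. The mode would still have to be stated consistently.
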